### Secondary outcomes for effectiveness evaluation

***Health-related quality of life ***will be measured with the Assessment of Quality of Life-6D (AQoL-6D) scale, which is composed of six domains (independent living, relationships, mental health, coping, pain, senses) [75]. The AQoL-6D has response scales that include 4–6 levels for each item, with higher scores indicating quality of life impairment. At baseline, the online survey included additional information for those still receiving inpatient treatment (“*For some questions, please imagine that you would have been at home if you are currently in the hospital*.”).

***Mental functioning*** will be measured with the 7-item Managing-scale and 6-item Cooperation/Communication scale from the Norwegian Function Assessment Scale (NFAS) [76]. The NFAS has a 5-point response scale, ranging from 1 (*no difficulty*) to 5 (*could not do it*). In accordance with [76], a response category item ‘*inapplicable to me, task not performed*’ was added and recorded as missing. The two NFAS subscale scores are each computed by calculating a mean score of the completed items, with low scores indicating good mental functioning [77].

***Overall job satisfaction*** will be measured with the following single-item question of the Job Satisfaction scale from the Copenhagen Psychosocial Questionnaire (COPSOQ) [78]: “*Regarding your work in general. How pleased are you with your job as a whole, everything taken into consideration?*” The single-item question has a 5-point response scale, with the answer options: *very satisfied*, *satisfied*, *unsatisfied*, *very unsatisfied*, and *not relevant*. However, we deleted the last response option and added ’*partly*’ as a third response option in between the scale to enable participants to respond neutrally to the question without forcing an answer in the positive or negative direction. The score of the single-item question ranges from 100 to 0, with higher scores indicating more job satisfaction.

***RTW self-efficacy*** will be assessed with the RTW self-efficacy scale (RTW-SE) [79], which was translated and verified in an earlier study [80]. The RTW-SE includes 11 items and has a 6-point response scale, ranging from 1 (*totally disagree*) to 6 (*totally agree*). A mean score over all 11 items is used to compute a total RTW-SE scale score, with higher scores indicating higher perceived self-efficacy regarding RTW.

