### Further variables

The following variables will be predominantly used as possible outcomes, covariates, moderators, or mediators within further exploratory analyses.

***Depressive symptoms*** will be measured with the Patient Health Questionnaire (PHQ-9) [87]. The PHQ-9 has a 4-point response scale, ranging from 0 (*not at all)* to 3 (*nearly every day*). The sum score ranges from 0 to 27, with higher scores indicating the severity of depressive symptoms.

***Interpersonal trust*** will be measured with the Interpersonal Trust Short Scale (KUSIV3) [88]. The KUSIV3 has a 5-point response scale, ranging from 1 (*do not agree at all*) to 5 (*completely agree*). The sum score ranges from 3 to 15, with higher scores indicating higher interpersonal trust.

***RTW expectation*** will be assessed with a single-item from the Screening Instrument Work and Occupation (SIBAR) [89]. The question was slightly adapted with respect to the study-specific setting at baseline (*“Considering your current state of health, when do you think you will be able to return to work after your discharge?”*). The SIBAR has a 7-point response scale, with the answer options: *immediately*, *one month*, *three months*, *six months*, *nine months*, *one year or later*, and *not at all anymore*. As has been done before [90], the single SIBAR-item responses will be dichotomised into a’positive RTW expectation (≤ 3 months)’ and’negative RTW expectation (> 3 months)’.

***Social support*** will be measured with the brief version of the Perceived Social Support Questionnaire (F-SozU K-6) [91]. The F-SozU K-6 has a 5-point response scale, ranging from 1 (*not true at all*) to 5 (*very true*). The sum score ranges from 6 to 30, with higher scores indicating higher levels of general perceived social support.

***Socio-demographics*** will be assessed at baseline (T0) with several items including information on *gender*, *age, education, marital status, cohabitation, residence, total number of inhabitants of the place of residence* (extra item asking for the *number of inhabitants younger than 14 years*) [92], *occupational status, company sector, monthly gross household income* [73]*, degree of disability* [89]*, ethnicity, migration* [93] and *distance to the practice of the respective therapist or other practitioners* [73]. Data on *household income* will be collected at all five measurement points for the health-economic evaluation.

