#### *Statistical analyses*

### Effectiveness evaluation

The primary outcome will be analysed using a logistic regression model to determine the odds ratio of the intervention effect. First, we will estimate a baseline model including treatment group (IG vs. CG) as a dummy-coded predictor variable and SRTW achievement as the outcome variable. Second, we will compute an adjusted estimate by including the stratification variable of the study centres as well as, if necessary, other socio-demographic variables for which differences between IG and CG occurred despite randomisation. Weighted effect coding will be considered for study centre, using the largest group as the reference group. Third, we will explore interaction effects between treatment group and all baseline assessments of the secondary outcomes and further variables. In case of statistically significant interaction effects, we will report intervention effects for different values of the covariates. In these and subsequent models, we will adopt a significance level of 5% for testing the focal parameters and report corresponding 95% confidence intervals (CIs).

In the context of the secondary analysis, multiple-group latent growth curve models (LGCM) will be estimated to investigate the effect of the intervention on changes in health-related quality of life, mental functioning, overall job satisfaction, severity of mental illness and work ability. LGCM are based on a structural equation modelling framework and allow for a more flexible adaptation to the specifics of the data structure than many multilevel models [100]. For each secondary outcome variable, we will include data at five time points and estimate a multiple group latent-basis model. This model is a less restrictive variant of the linear growth curve model, i.e. it contains a latent intercept for baseline differences and a latent slope for change differences, but can also represent nonlinear forms of change. If necessary, we will allow the residual variances to differ between treatment groups and time points. The focal parameter in each model is the mean difference of the latent slopes between treatment groups.

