In addition, we will explore several baseline variables as prognostic and prescriptive predictors of change. To do this, we will use the EffectLiteR approach and consider baseline variables in the multiple-group LGCM [101]. The focal test for potential prescriptive variables is an omnibus test for interactions between treatment group and baseline variables. All model parameters are estimated using full information maximum likelihood. To account for possible deviations from a normal distribution in outcome variables, we use scaled test statistics and robust standard errors.

All data will be analysed according to the intention-to-treat principle. Missing data for the primary and secondary outcomes are assumed to be “missing at random” (i.e. missing at random conditional on information from all variables included in the respective model). To make this assumption plausible, we will first correlate all baseline variables with the missingness of data at later time points, and then include all baseline variables that predict missingness in the estimation of focal parameters. For the analysis of the primary outcome, we will implement this using multiple imputation by chained equations (MICE) [102]. For the analyses of the secondary outcomes, we will use an auxiliary variables approach [103].

A per-protocol approach for the following two pre-defined IG subgroups will be conducted as sensitivity analyses: (1) for those who had attended at least 3 out of 8 Module A sessions, 6 out of 9 Module B sessions, as well as 1 out of 3 video call session(s) within Module C; and (2) for those who have provided their data at all measurement time assessments (T0-T4). Another sensitivity analysis will be conducted to investigate different diagnostic patient subgroups (e.g. CMDs (F3, F4) vs. all others).

Further details of the statistical analyses will be determined in an analysis plan, which will be pre-registered via the Open Science Framework [104] before database closure. Additional quality assurance and monitoring by an independent statistical expert will be considered throughout the project period. All effectiveness evaluation analyses will be performed using the statistical platform R 4.1 or higher.

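### Moderator screening on the primary outcome uses about 25 unadjusted 5% interaction tests, so at least one false covariate-specific effect would be expected in roughly 60–70% of trials with no true effect modification

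*Protocol article*

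**What the plan says.** The primary outcome is analysed by logistic regression in three steps (Protocol article, Statistical analyses, Effectiveness evaluation). The first fits treatment group alone. The second adds study centre and, if needed, unbalanced socio-demographic variables. In the third, "we will explore interaction effects between treatment group and all baseline assessments of the secondary outcomes and further variables". The consequence follows at once: "In case of statistically significant interaction effects, we will report intervention effects for different values of the covariates". For these and all later models, "we will adopt a significance level of 5% for testing the focal parameters", with matching 95% confidence intervals.

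No short list of moderators, global test or multiplicity adjustment is stated for this step.

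The candidates are found in two other sections. Secondary outcomes for effectiveness evaluation lists the secondary measures. Further variables lists four more baseline scales and the socio-demographic items, and opens by saying: "The following variables will be predominantly used as possible outcomes, covariates, moderators, or mediators within further exploratory analyses".

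For the secondary-outcome growth models, the same analysis section describes a different approach: "The focal test for potential prescriptive variables is an omnibus test for interactions between treatment group and baseline variables". Further statistical detail is deferred to an analysis plan to be pre-registered before database closure.

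**The concern.** The article fixes three things together: a wide candidate set, a 5% threshold, and a reporting consequence that follows from crossing it. That is a decision rule, and its error rate can be calculated. With many tests and no adjustment, at least one crossing is likely even when the effect is identical in all patients.

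Selection by significance also distorts size. The trial is powered at 80% for the main effect only, so power for interactions is lower. Those that pass p<0.05 will tend to be overestimates.

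At stake is the interpretation of the primary outcome across patient groups. The Discussion foresees adoption into standard care if results are promising, so covariate-specific effects shown for a chance moderator could influence who is thought to benefit.

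**Working it through.** The article states no error rate for this step, so there is no such figure to reproduce. Its sample-size figures fix the sample sizes used below, so they come first.

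**1. Sample size (Sample size and power calculation).** The inputs are 60% vs 75%, two-sided 5%, power 80% and 1:1 allocation.

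n per arm = [1.960·√(2·0.675·0.325) + 0.842·√(0.60·0.40 + 0.75·0.25)]² / 0.15² = 151.9, so 152. This matches the article. With 40% drop-out, 304/0.6 = 506.7, against a stated 506. The calculations therefore use N=304 (completers) and N=506 (all randomised, as after imputation).

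**2. Number of tests.** Each listed item is counted once.
- Seven secondary-outcome scores: AQoL-6D, two NFAS scales, job satisfaction, RTW-SE, BSI-18 and WAS. NFAS counts twice because "The two NFAS subscale scores are each computed by calculating a mean score of the completed items".
- Four further scales: PHQ-9, KUSIV3, RTW expectation and F-SozU K-6. Treatment satisfaction is left out because it is measured after treatment has begun.
- Fourteen socio-demographic items: gender, age, education, marital status, cohabitation, residence, number of inhabitants, occupational status, company sector, household income, degree of disability, ethnicity, migration and distance to the practitioner.

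The total is 7 + 4 + 14 = 25, or 26 with the extra item on inhabitants under 14. AQoL-6D domains, BSI-18 subscales or job characteristics would raise it.

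**3. Independent tests, no true interaction.** P(at least one p<0.05) = 1 − 0.95^m.

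| m | Probability |
|---|---|
| 11 (scales only) | 43% |
| 22 | 68% |
| 25 | 72% |
| 26 | 74% |

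The expected number of false interactions for m = 25 is 25 × 0.05 = 1.25.

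**4. Correlated tests.** The correlations are assumed, since the article gives none. With the 11 scales correlated at 0.3, 0.5 or 0.7 and all other pairs uncorrelated, 25 tests give 69%, 66% and 62%. Setting all other pairs to 0.1 gives 68%, 65% and 61%. The 11 scales alone give 38%, 30% and 22%.

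**5. Simulated logistic models.** Data had 60% vs 75% success, no interaction, 11 scales correlated at 0.5 and 14 independent items. One model was fitted per moderator, with 400 runs per setting.
- At least one p<0.05 occurred in 65% of trials at N=304 and 67% at N=506. The Monte Carlo standard error is √(0.66·0.34/400), about 2.4 percentage points.
- Rejection rates per test were 0.0502 and 0.0479, so 25 × these = 1.26 and 1.20 false interactions per trial.
- Correlating the socio-demographic items at 0.3 lowers the rate to about 62%. Across the simulations with separate models the range is 59–68%.
- If all 25 interactions enter one model, the rate is about 82%, partly because the Wald tests are then anti-conservative.

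**6. Effect of adjustment.** With no true interaction, Holm makes a false claim only if the smallest p-value is below 0.05/25 = 0.002. For independent tests, 1 − 0.998^25 = 4.9%. In simulation the rate was 3 to 5%.

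**7. An omnibus gate as an alternative.** A likelihood-ratio test of 25 interactions in one logistic model, with no true interaction (2,000 runs), rejected in about 15% of trials at N=304 and 9–11% at N=506, not 5%.

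**The case against.** The strongest reply is that the step is exploratory and says so. Unadjusted moderator screening under that label is common, the primary treatment test keeps its type I error, and multiplicity detail can be left to the analysis plan. Most of this stands, and it limits the weight of the point. It does not remove it. The article does more than leave a gap: it states a threshold and a reporting consequence, and that rule has the error rate shown.

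The count can also be challenged. The article gives no number of tests and does not say that each moderator gets its own model. Some further variables may serve only to describe the sample. This stands too. With the 11 scales alone the rate is about 30%, still well above 5%.

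A reader might infer three stronger things that the text does not support:
- **That non-significant interactions would go unreported.** The article does not say this. It promises 95% confidence intervals for focal parameters, which may be read as covering every interaction. It only lacks an explicit commitment.
- **That the trial will probably claim the intervention works for some employees and not others.** Showing effects at several covariate values is the usual way to interpret an interaction and is not itself such a claim.
- **That the secondary outcomes have a proper gate and the primary outcome does not.** The omnibus test is called focal within each growth model, but nothing says it must be passed before single interactions are examined.

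**Conclusion.** The point holds as a weakness in the stated rule for presenting effect modification on the primary outcome. With no true effect modification, covariate-specific effects would be triggered in roughly 60–70% of trials when about 25 moderators are tested in separate models, with 1.2 to 1.3 false interactions expected. If only the 11 scales are tested, the rate is about 30%.

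These figures rest on a count taken from the article's lists without sight of its Table 2, on one test per item, and on assumed correlations. The unseen analysis plan may add a correction.

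The confirmatory conclusion is not at risk. It would be wrong to read this as inflation of the primary test or as proof of selective publication. It is a moderate point that is cheap to correct.

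**What to change.** In the third step of the primary analysis, or in the analysis plan still to be registered, replace the reporting sentence with wording such as:

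> The number of treatment-by-baseline interactions tested on SRTW will be stated, and each will be reported with its estimate and 95% CI whatever its p-value. Covariate-specific intervention effects will be presented as evidence of effect modification only where the interaction is significant after Holm adjustment over all interactions tested. Other nominally significant interactions will be labelled hypothesis-generating.

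Do not replace this with a gate based on an asymptotic omnibus likelihood-ratio test of all 25 interactions, which is anti-conservative at these sample sizes. If a global test is wanted, calibrate it under a no-interaction model, for example by permutation.

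The cost is a few sentences and one supplementary table, with no new data. The downside is less power to single out an individual moderator.

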**Methods:**

The study consists of an effectiveness, a health-economic and a process evaluation, designed as a two-armed, multicentre, randomised controlled trial, conducted in German psychiatric outpatient clinics. Sick-listed employees with MDs will receive either the 18-month RTW-PIA treatment in conjunction with care as usual, or care as usual only. RTW-PIA consists of a face-to-face individual RTW support, RTW aftercare group meetings, and web-based aftercare. Assessments will be conducted at baseline and 6, 12, 18 and 24 months after completion of baseline survey. The primary outcome is the employees´ achievement of sustainable RTW, defined as reporting less than six weeks of working days missed out due to sickness absence within 12 months after first RTW. Secondary outcomes include health-related quality of life, mental functioning, RTW self-efficacy, overall job satisfaction, severity of mental illness and work ability. The health-economic evaluation will be conducted from a societal and public health care perspective, as well as from the employer’s perspective in a cost–benefit analysis. The design will be supplemented by a qualitative effect evaluation using pre- and post-interviews, and a multimethod process evaluation examining various predefined key process indicators from different stakeholder perspectives.

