### *Allocation and blinding*

Patients will be randomly assigned to either IG or CG with a 1:1 allocation, using permuted block randomisation with varying sizes stratified by study centre. Before recruitment began, five randomisation lists were prepared via an online randomisation service [72] by an independent researcher, blinded to the study conditions. For adequate allocation concealment, the generated lists were then securely transferred to an independent administrative working group, to which the evaluators, clinical practitioners, and participants never have access during recruitment. The baseline assessment takes place before group allocation to minimise reporting and selection bias. After completion, all participants will be randomised according to their chronological order of survey participation. The respective randomisation date will serve as the participant´s admission to the study. Blinding among study participants and treatment providers will not be possible before, during, or after the study. Due to the questionnaire design with items concerning the individual intervention modules, the evaluators will also not be blinded.

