#### Sample size and power calculation

In order to demonstrate a 15% increase in the proportion of employees from the IG achieving SRTW, based on [80] (CAU: 60%; RTW-PIA: 75%; power: 80%; significance level: 5%), the required sample size will be a minimum of 152 study participants per study arm. Calculations were performed with a sample size software [98]. Following previous authors [58, 99], we assumed a drop-out rate of 40%; thus, 506 participants will be needed in total.

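### The secondary growth-curve models, read naturally, estimate a baseline mean per arm although baseline precedes randomisation, which usually costs precision; their outcome list also omits RTW self-efficacy

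*Protocol article*

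**What the plan says.** In the Protocol article, under Statistical analyses, Effectiveness evaluation, the secondary outcomes are to be analysed with multiple-group latent growth curve models over five time points. The model is a latent-basis variant of the linear growth curve, and the text explains that "it contains a latent intercept for baseline differences and a latent slope for change differences". The focal parameter is the difference between arms in the mean latent slope. Nothing is said about constraining the intercept means across arms.

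The section Allocation and blinding fixes the order of events: "The baseline assessment takes place before group allocation to minimise reporting and selection bias". The section Recruitment procedure agrees: consent, then the baseline survey, then randomisation.

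On the outcomes, the abstract names six secondary outcomes: "health-related quality of life, mental functioning, RTW self-efficacy, overall job satisfaction, severity of mental illness and work ability". The section Secondary outcomes for effectiveness evaluation describes the same six, and scores RTW self-efficacy as a mean of 11 items. The sentence introducing the growth models lists "changes in health-related quality of life, mental functioning, overall job satisfaction, severity of mental illness and work ability", which is five. A later sentence in the same paragraph says that the model is fitted for each secondary outcome variable.

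**The concern.** In a multiple-group model, an intercept described as carrying baseline differences, set beside a slope carrying change differences, most naturally means one intercept mean per arm. The slope contrast then compares change from each arm's own estimated baseline. Because allocation follows baseline, the population difference at T0 is known to be zero. Estimating it discards that knowledge, and noise in the observed baseline difference passes into the estimated slope difference. The other uses of baseline variables do not restore this: the baseline predictors of change are exploratory, and the auxiliary variables serve the missing-data assumption.

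What is at stake is the width of the intervals for the secondary outcomes, in a trial that expects 40% drop-out.

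The list mismatch is a separate matter. RTW self-efficacy is something that the modules are meant to strengthen, and participants, providers and evaluators are all unblinded. Whether and how its effect is tested should not be open to two readings.

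**Working it through.** **The plan's own figure.** The inputs are "CAU: 60%; RTW-PIA: 75%; power: 80%; significance level: 5"%, with 1:1 allocation. The two-sided pooled formula gives n = [1.960·√(2·0.675·0.325) + 0.8416·√(0.6·0.4 + 0.75·0.25)]² / 0.15² = (1.2982 + 0.5503)² / 0.0225 = 151.9. This agrees with "the required sample size will be a minimum of 152 study participants per study arm". For drop-out, 304/0.6 = 506.7, against "we assumed a drop-out rate of 40%; thus, 506 participants will be needed in total"; the difference is rounding. This calculation concerns the primary outcome only. The protocol gives no standard deviation, correlation or precision for any secondary outcome, so everything below rests on assumed variance components.

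**Single follow-up.** Let ρ be the correlation between baseline and follow-up, with equal variances. Separate baseline means give a change-score contrast with variance proportional to 2(1−ρ). A common baseline mean gives 1−ρ². The ratio is (1+ρ)/2.

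| ρ | Variance ratio, common/separate | SE wider with separate means |
|---|---|---|
| 0.3 | 0.65 | 24% |
| 0.5 | 0.75 | 15% |
| 0.7 | 0.85 | 8% |

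At ρ = 0.5, a comparison with 80% power under a common mean has Φ(2.802·√0.75 − 1.960) = Φ(0.466), or about 68%, with separate means.

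**Five occasions, loadings treated as known.** Write Λ for the intercept and slope loadings, Ψ for the latent covariance matrix and θ for the residual variance. Per participant, the estimated (intercept, slope) pair has covariance V = Ψ + θ(Λ′Λ)⁻¹. With equal arms, forcing a common intercept mean multiplies the variance of the slope difference by 1 − V₁₂²/(V₁₁V₂₂). Assume intercept variance 0.6 and θ = 0.4.

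- Linear loadings (0, 0.25, 0.5, 0.75, 1): θ(Λ′Λ)⁻¹ has entries 0.24, −0.32 and 0.64. With slope variance 0.8 and correlation 0, the ratio is 1 − 0.32²/(0.84·1.44) = 0.915.
- Early-change loadings (0, 0.5, 0.8, 0.95, 1): the entries are 0.3285, −0.3824 and 0.5882. With slope variance 0.3 and correlation −0.5, the covariance is −0.2121 − 0.3824 = −0.5945. The ratio is 1 − 0.5945²/(0.9285·0.8882) = 0.571.
- These two are the extremes for slope variance 0.3 to 0.8 and correlation 0 to −0.5. The common-intercept model therefore has about 8% to 43% less variance.
- Linear loadings, slope variance 0.8, correlation +0.3: the covariance is 0.2078 − 0.32 = −0.1122, and the ratio is 0.990. At correlation +0.46 it is 1.000. The gain vanishes there; the ratio never exceeds 1.

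**Five occasions, loadings and (co)variances estimated, 253 per arm.** Twenty-four scenarios were run: intercept reliability at T0 of 0.3 to 0.7, slope variance 0.2 or 0.5, and correlation −0.5 to +0.3. With free intercept means the SE of the slope difference was 0.6% to 46% wider with complete data, and 0.8% to 38% wider with 40% monotone drop-out. In a middle case (reliability 0.5, slope variance 0.2, correlation 0) the SEs were 0.0900 against 0.0783 (15% wider), and with drop-out 0.1043 against 0.0925 (13% wider).

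**Outcome count.** The abstract and the outcome section give six; the growth-model list gives five. The one missing is RTW self-efficacy. Being a mean score, it would suit the same model.

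**The case against.** The protocol never literally says that the intercept means are free by arm. The clause could be describing what any growth model contains, and further statistical detail is deferred to an analysis plan to be pre-registered before database closure. That is fair, and it is why the point rests on the natural reading rather than on an explicit statement. Against it stand the multiple-group form, the wording about baseline differences and the choice of focal parameter, all of which point the same way.

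Free means are also not an error. A reader might infer that chance imbalance biases the secondary effects. It does not: over randomisations the slope contrast is unbiased, and the imbalance is sampling variation already contained in the standard error. Nor can one say that every secondary comparison loses materially. The 8% lower end reflects zero or negative intercept-slope correlations; at clearly positive ones the loss is about nil.

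Finally, a reader might infer that RTW self-efficacy will have no effect analysis. The sentence applying the model to each secondary outcome variable plausibly covers it, so the documents support only a mismatch with the explicit list. The schedule in Table 2 is not shown here. It has a footnote for items asked only after return to work, and whether that touches this scale cannot be judged.

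**Conclusion.** The point stands as one of efficiency and clarity, not validity. On the natural reading, the secondary models estimate a baseline difference that randomisation after baseline already sets to zero. Under the assumed variance components, removing it cuts the variance of the slope difference by about 8% to 43% when intercept and slope are uncorrelated or negatively correlated, and by about nothing when they are clearly positively correlated. Which case applies to which outcome cannot be read from the documents. The RTW self-efficacy omission is an inconsistency between the explicit five-item list and the six named outcomes, and needs no assumptions to see. The logistic regression for the primary outcome and the sample size of 506 are untouched.

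**What to change.** In the analysis plan, constrain the latent intercept means to be equal across arms in each secondary growth model, or regress the latent slope on the latent intercept, and test the between-arm slope difference in that model.

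Add RTW self-efficacy to the list of growth-model outcomes so that the list agrees with the sentence covering each secondary outcome. If the schedule does not measure it at all five time points in all participants, say so and state the comparison to be made.

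The cost is one equality constraint and one added outcome. No new data are needed, and the change can be made before the plan is registered.

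### With 40% drop-out planned, the article names only baseline predictors of missingness to support imputation of the primary outcome, and none of its stated sensitivity analyses tests that assumption

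*Protocol article*

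**What the plan says.** All references are to the protocol article.

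- **Sample size and power calculation.** "the required sample size will be a minimum of 152 study participants per study arm", and "we assumed a drop-out rate of 40%; thus, 506 participants will be needed in total".
- **Statistical analyses, Effectiveness evaluation (missing data).** Analysis is by intention to treat. Primary and secondary outcomes are assumed MAR given the variables in each model. To support this, "we will first correlate all baseline variables with the missingness of data at later time points"; the baseline variables found to predict missingness are then included. For the primary outcome this is done by multiple imputation by chained equations (MICE). No post-baseline variable is named.
- **Same section (sensitivity analyses).** "A per-protocol approach for the following two pre-defined IG subgroups will be conducted as sensitivity analyses". The first subgroup is defined by attendance at Modules A, B and C. The second is "for those who have provided their data at all measurement time assessments (T0-T4"). A further sensitivity analysis looks at diagnostic subgroups. Other details go to an analysis plan to be pre-registered before database closure.
- **Primary outcome, items (I) and (II).** Return to work is asked at each of T1 to T4, returners give the date, and they are asked whether sickness absence since then has exceeded six weeks.
- **Statistical analyses, primary model.** Logistic regression on treatment group, then adjusted for study centre and, if needed, socio-demographic variables.

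**The concern.** The article states a selection rule for the imputation, and the rule looks in the wrong place in two respects. It searches only baseline variables, and it picks them for their link with missingness, not with SRTW. A variable that predicts missingness but not the outcome does nothing against bias. A variable that predicts both does, and the strongest candidates here are post-baseline: whether and when someone returned, and whether they had already relapsed. These are components of the outcome itself.

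The secondary outcomes are better placed. Their growth models use all five time points under full information maximum likelihood, so the earlier scores of someone who leaves still inform the fit. The primary model has one binary outcome and baseline covariates, so interim information enters only if it is put into the imputation.

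The stated sensitivity analyses do not fill the gap. The attendance set concerns exposure to treatment. The T0-T4 set keeps only people who did not drop out. The diagnostic analysis does not concern attrition. The T0-T4 set is also worded as an intervention-group (IG) subgroup. If IG completers are set against an unselected control group (CG), selection acts on one arm only.

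At stake is the primary odds ratio, with up to two fifths of outcomes imputed.

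**Working it through.** **1. The plan's own figures.** Inputs: 60% vs 75%, power 80%, significance level 5% (sidedness not stated).

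n = [1.960·√(2·0.675·0.325) + 0.842·√(0.24 + 0.1875)]² / 0.15² = 151.9, so 152 per arm (two-sided, no continuity correction; one-sided would give 120).

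Drop-out: 304 / 0.60 = 506.7, against 506 stated (2 × 253). The sample size is not in error. Observed outcomes per arm: 253 × 0.60 ≈ 152, leaving about 101 to impute.

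**2. Closed-form check of bias.** The documents give no drop-out by arm or by return-to-work state, so these inputs are assumptions:
- SRTW is 86% in a good interim state and 12% in a poor one.
- True SRTW is 60% CG and 73% IG, a true odds ratio of (0.73/0.27)/(0.60/0.40) = 1.80.
- Drop-out is 34% in the good state in both arms.
- The included baseline variables carry no information about SRTW, so imputation reproduces each arm's observed rate.

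Share in the good state, g = (p − 0.12)/0.74: CG 0.649, IG 0.824.

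Observed rate = 0.12 + 0.74·[0.66g / (0.66g + r(1 − g))], where r is retention in the poor state.

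| Poor-state drop-out | CG rate | IG rate | Difference (points) | Odds ratio |
|---|---|---|---|---|
| Truth | 60.0% | 73.0% | 13.0 | 1.80 |
| CG 65%, IG 45% | 69.5% | 74.8% | 5.4 | 1.31 |
| CG 45%, IG 65% | 63.0% | 78.5% | 15.5 | 2.14 |
| 50% in both | 64.5% | 75.7% | 11.2 | 1.72 |

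Overall drop-out in the three scenarios lies between 36% and 45% per arm. If drop-out depends on the final outcome identically in both arms (retention 70% in achievers, 45% in non-achievers; true 60% vs 75%), the odds ratio stays at 2.00, though the risk difference falls from 15 to 12 points.

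**3. Does the interim information help?** Simulation of 1,000 trials per scenario, 253 per arm, no treatment effect, SRTW about 60%, overall drop-out about 40%. CG retention is 60% throughout. IG retention depends on return to work by T1.

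| IG retention, early returners vs others | Baseline-only imputation: bias, false positives | With T1 return to work: bias, false positives |
|---|---|---|
| 60% vs 60% | +0.2 points, 6.1% | +0.2 points, 4.4% |
| 70% vs 50% | +4.0 points, 12% | +0.1 points, 5.7% |
| 80% vs 40% | +7.8 points, 31% | +0.1 points, 5.4% |

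Interim status removes the bias here because drop-out was made to depend on it and it was observed for everyone. People lost before T1 contribute no interim data, so the real gain depends on when drop-out occurs.

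**4. One-arm completer set.** Take no effect, 60% SRTW in both arms, and retention of 70% in achievers and 45% in non-achievers. Completers then show 0.6·0.70 / (0.6·0.70 + 0.4·0.45) = 70%. Against an unselected CG at 60% this is a spurious +10 points. With the same selection in both arms it is 70% vs 70%, no difference.

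**The case against.** Several points on the other side stand.

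- **The article does not say that only baseline variables are used.** A reader might infer that T1-T3 data are excluded. The text names none, but it does not forbid them. MICE is built for several incomplete variables, and the article does not say whether it is applied to the outcome components or to the derived yes/no.
- **Bias is conditional.** If missingness depends only on the included baseline variables, the stated method removes it. If drop-out follows the same pattern in both arms, the odds ratio, which is the primary effect measure, moves little or not at all. Differential drop-out is an assumption.
- **No direction is established.** A reader might infer that attrition flatters RTW-PIA and that the IG subsets would then seem to confirm the result. The table does not support that: if controls doing badly leave more often, the primary result is biased against the intervention.
- **The comparator for the IG subgroups is not stated**, so the one-arm comparison is a risk of the wording, not a declared plan. Attendance can only be defined in the IG, and both sets are labelled sensitivity analyses beside an intention-to-treat primary analysis.
- **Further details are deferred to the analysis plan.** The absence of a delta-adjusted analysis or of a full auxiliary list is therefore not a fault of the article.

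The deferral does not dispose of the point. The selection rule and the completer definition are stated, and an analysis plan that simply follows them inherits both weaknesses.

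**Conclusion.** The point holds in a limited form. For a primary outcome with 40% planned drop-out, the article rests MAR on baseline variables chosen for predicting missingness. It names none of the collected T1-T3 return-to-work, relapse or secondary-outcome data, and it states no sensitivity analysis that tests MAR. Its completer set is worded for one arm although survey completion applies to both.

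Under the assumed patterns, a true odds ratio of 1.80 could be estimated anywhere from 1.31 to 2.14 when drop-out among those doing badly differs by 20 percentage points between arms. With no true effect, false positives could reach 12% to 31%. With equal drop-out patterns the bias is small or absent. Differential drop-out is plausible because participants are not blinded (Allocation and blinding) and only the IG is offered up to 20 additional sessions (RTW-PIA in conjunction with CAU), but no figure in the article establishes it. The documents do not support the stronger conclusions that the primary analysis is biased, or biased towards RTW-PIA.

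**What to change.** In the analysis plan, before database closure:

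1. Put T1-T3 return-to-work status and date, interim relapse answers and secondary-outcome scores into the imputation model, together with baseline variables that predict SRTW as well as those that predict missingness. Impute separately by arm.
2. Define the T0-T4 completer analysis for both arms, and report it as a completer analysis, not as adherence. This removes one-arm selection but does not protect against drop-out patterns that differ by arm.
3. State the comparator for the attendance subset and interpret the result as a non-randomised comparison.
4. Optionally, add a delta or tipping-point analysis by arm. For scale: if 60% vs 75% is observed with 40% missing and CG drop-outs achieve 60%, the difference is 9 points if IG drop-outs achieve 60%, and zero at (0.60 − 0.60·0.75)/0.40 = 37.5%.

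The cost is analysis-plan wording and programming. No new data collection and no change in sample size are needed.
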